##### Secondary outcomes

2. Ability to walk independently

As measured by the Functional Ambulation Categories (FAC) [32]. This scale is designed to give detail on physical support needed by patients for walking, so has clinical relevance, and is easy to use. It has established validity and reliability for use after stroke [38]. It is an ordinal scale, patients scoring from 0-5, where 0 indicates a patient who is not able to walk or needs help of 2 therapists, and 5 indicates a patient who is independent in ambulation even on stairs.

3. Onset and offset of EMG activity of antagonistic muscle groups during pedalling

EMG activity will be recorded in quadriceps and hamstring muscles for each leg. Before getting on the bike, participants will have a small (37 mm × 18 mm) pre-amplifier applied to the front and back of their thigh on both sides, following skin preparation to minimise signal interference. Electrode position is known to be a vital factor in achieving accurate EMG information [39]. For this study, a single researcher will place the electrodes for each participant and for every session, using published guidelines [40]. When the participants are positioned comfortably on the bike, the leads from the pre-amplifiers will be connected as described in *instrumentation*.

Resting EMG activity will be recorded as a voltage at 1,000 Hz whilst the participant's foot is resting firmly on a box so that the leg is still and supported with the knee in 5-15 degrees of flexion, for 30 seconds. This will be undertaken for each leg. EMG data (voltage) will be collected continuously during pedalling for a minimum of 30 seconds at approximately 50 rpm.

Baseline EMG values will be calculated from the rectified, processed signal as the mean ± 3 SD (standard deviations) during the 30 seconds baseline data collection period. Onset of activity in each of the four muscle groups will be defined as the time point during the 360 degree turn at which EMG voltage exceeds the mean baseline value plus 3SD for 20 consecutive data points (20 ms). Offset of activity in each of the four muscle groups will be defined as the time point during the 360 degree turn at which EMG voltage falls below the mean baseline value minus 3SD for 20 consecutive data points (20 ms). The time point for onset and offset of muscle activity in each of the four muscle groups will also be recorded as a function of the position of the pedal during the 360 degree turn.

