4. Reciprocal activation of antagonistic muscle groups (muscle activity) during pedalling

Rectified EMG data for each antagonistic muscle group will be analysed using Spearman's correlation coefficient. An r value of 1.0 indicates perfect positive correlation and therefore complete co-contraction, no reciprocal activation, of an antagonistic muscle pair. An r value of 0 indicates no correlation and therefore no relationship between EMG activity of an antagonistic muscle pair. An r value of -1.0 indicates a perfect negative correlation and therefore complete reciprocal activation of antagonistic muscle groups.

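### Spearman's r on rectified EMG is read as if complete alternation scored -1, but on unsmoothed samples it scores at most about -0.75 in size and shifts with burst amplitude and burst length

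*Protocol article*

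**What the plan says.** Item 4 under Secondary outcomes of the protocol article defines the score: "Rectified EMG data for each antagonistic muscle group will be analysed using Spearman's correlation coefficient". It then gives a meaning to three points of the scale. At the top, "An r value of 1.0 indicates perfect positive correlation and therefore complete co-contraction, no reciprocal activation, of an antagonistic muscle pair". In the middle, "An r value of 0 indicates no correlation and therefore no relationship between EMG activity of an antagonistic muscle pair". At the bottom, "An r value of -1.0 indicates a perfect negative correlation and therefore complete reciprocal activation of antagonistic muscle groups". No filter, envelope or averaging over turns is stated for this outcome.

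The preceding item, on onset and offset, describes the recordings: "EMG data (voltage) will be collected continuously during pedalling for a minimum of 30 seconds at approximately 50 rpm". The sampling rate is given for the resting recording ("Resting EMG activity will be recorded as a voltage at 1,000 Hz"). The onset rule treats 20 data points as 20 ms, so the same rate evidently applies during pedalling. That item also mentions processing, but only for the resting baseline and without defining it: "Baseline EMG values will be calculated from the rectified, processed signal".

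Under Aims, reciprocal activation is one of four criteria of clinical efficacy. Under Experimental Intervention it is recorded at every session. Under Statistical Analysis, follow-up measures are compared between arms and changes are tested within groups.

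**The concern.** Rectified surface EMG behaves like noise within a burst. While one muscle is active and its antagonist is quiet, the individual sample values of the two are unrelated. Only the on/off contrast contributes to a rank correlation, so complete alternation need not give -1, nor complete co-contraction +1. How much the contrast contributes depends on two things other than reciprocity: how far bursts stand above resting level, and what share of the turn each muscle is active.

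The therapy aims to increase voluntary contraction of paretic muscle. If stronger contraction gives larger bursts (a plausible assumption that the article does not state), r could become more negative with timing unchanged, and the stated scale invites reading that as better reciprocal activation. Conversely, weak but perfectly alternating muscles could score near 0, which the article equates with no relationship.

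**Working it through.** **Inputs from the article.** Rectified EMG; Spearman's r; 1,000 Hz; at least 30 s at about 50 rpm, which is 60/50 = 1.2 s per turn, 30/1.2 = 25 turns and 30,000 samples. The stated value for complete reciprocal activation is -1.0.

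**Assumptions, because the article gives no values.** Square bursts half a turn apart that never overlap, each filling share d of the turn (d ≤ 0.5); burst amplitude k times rest; Gaussian EMG, independent between muscles; no smoothing.

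**Can -1.0 be reproduced?** Only in idealised cases. Noise-free antiphase sine envelopes give -1.00. Noise-free on/off signals give -d/(1-d), which is -1 at d = 0.5 but -0.3/0.7 = -0.43 at d = 0.3.

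**Limit for very large k.** Scale ranks to run from 0 to 1 (mean 1/2, variance 1/12). Active samples fill the top share d, so their mean rank is (1-d)/2 above 1/2. Resting samples lie on average d/2 below it.

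- Alternation: covariance = 2d × [(1-d)/2] × [-d/2] + (1-2d) × d²/4 = -d²/4. Dividing by 1/12 gives r = -3d².
- Simultaneous bursts: covariance = d × (1-d)²/4 + (1-d) × d²/4 = d(1-d)/4, so r = 3d(1-d).

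| d | alternation, -3d² | simultaneous, 3d(1-d) |
|---|---|---|
| 0.5 | -0.75 | 0.75 |
| 0.4 | -0.48 | 0.72 |
| 0.3 | -0.27 | 0.63 |

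**Finite k.** Let P be the chance that a rectified burst sample exceeds a rectified resting sample. For Gaussian signals P = (2/π) × arctan(k). Both deviations above shrink by the factor (2P-1), so r = -3d²(2P-1)².

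- k = 2: P = 0.705, (2P-1)² = 0.168. At d = 0.5, r = -0.75 × 0.168 = -0.13. At d = 0.3, r = -0.27 × 0.168 = -0.05.
- k = 10: P = 0.937, (2P-1)² = 0.762. At d = 0.5, r = -0.57. At d = 0.3, r = -0.21.
- k = 100: P = 0.994, (2P-1)² = 0.975. At d = 0.5, r = -0.73. At d = 0.3, r = -0.26.

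Simulation of 30 s at 1,000 Hz with band-limited Gaussian signals agrees to within about 0.01. Half-sine bursts of 50% give smaller values: -0.06 at k = 2 and -0.42 at k = 10. Two continuously co-active muscles give about 0.

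**With a low-pass envelope (simulation, alternating square bursts).**

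- 50% bursts, 20 Hz: about -0.76 to -0.78, almost flat across k.
- 50% bursts, 3 Hz: up to about -0.93.
- 30% bursts, 20 Hz: about -0.27.
- 20% bursts, 3 Hz: from -0.23 at k = 1.5 to +0.22 at k = 100.

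With half-sine 50% bursts at 20 Hz some amplitude dependence remains: -0.57 at k = 2 and -0.74 at k = 10.

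**The case against.** The strongest reply is that the figures belong to one processing chain. The article says rectified, not rectified and unsmoothed. The neighbouring item speaks of a processed signal, and filter settings are commonly left to a fuller document. A reader might infer from the algebra that r can never approach -1, or that any change in r is merely signal strength. The article supports neither: with a slow envelope and long bursts r reaches about -0.93, and a 20 Hz envelope makes it nearly independent of amplitude for 50% square bursts. This part of the objection stands, and it limits the point to the score as written.

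A reader might also infer that the quoted sentence is false. Read literally it is not, since r = -1 would indeed mean perfectly opposed activity. What fails is the converse, on which the scale relies: complete alternation does not yield -1.

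The article sets no threshold or decision rule on r. Both arms use the same score, timing is a separate outcome, and the trial is an early-phase study of 24 participants that does not claim to demonstrate efficacy definitively. All of this limits the consequence. It does not remove it: the score feeds a named efficacy criterion, a shared score does not protect a comparison if arms differ in burst size or length, and dependence on burst share persists after smoothing.

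**Conclusion.** The point holds for the outcome as the article words it. On unsmoothed rectified EMG, complete alternation gives at most 0.75 in size with bursts of half a turn and 0.27 with bursts of 30%. At 50% bursts, a rise in amplitude from 2 to 10 times rest moves r from about -0.13 to -0.57 with no change in timing. Simultaneous bursts reach at most 0.75 or 0.63. The score therefore mixes reciprocity with signal strength and burst length, and the meanings given to -1, 0 and +1 mislead.

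The sizes depend on the assumed burst shape, burst share, amplitude ratio and absence of smoothing, none of which the article gives. They show sensitivity and do not predict this trial's values. Smoothing largely cures the amplitude effect for long square bursts, but not the dependence on burst share. This is a defect in a secondary outcome that is worth correcting; it does not show that the EMG recordings are unusable.

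**What to change.** 1. Compute the correlation on a smoothed (low-pass) envelope instead of raw rectified samples, with filter type and cut-off fixed in advance. The results above show that the cut-off matters.
2. Delete the statements that -1, 0 and +1 mean complete reciprocal activation, no relationship and complete co-contraction.
3. Interpret any change or difference in r together with each muscle's active share of the turn, taken from the onset/offset outcome. This needs a workable offset threshold: the article puts offset below the resting mean minus 3 SD, a level that a muscle simply returning to rest would not be expected to reach.
4. Optionally add a supporting overlap index per leg: the share of the turn with both muscles active divided by the share with either active. Calculate it only for turns in which both muscles cross the onset threshold, and report the number of excluded turns by arm. Without that restriction the index scores 0, apparently fully reciprocal, when one muscle never crosses, and is undefined when neither does.

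The cost is a script change and one paragraph, with no new data. The downside is that some turns in severe paresis will not be scorable for the overlap index.

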#### Prognostic indicator measures

5. Site of stroke lesion

The location and size of stroke lesion have been demonstrated to be a prognostic factor for functional outcomes after stroke [28,29]. It is possible, therefore, that this clinical factor might be linked to the ability to take part in rehabilitation interventions. Brain lesion location will therefore be recorded from the clinical scan.

6. Degree of muscle weakness as measured by the Motricity Index (see clinical efficacy measures)

7. Ambulatory Capacity as measured by the Functional Ambulatory Categories (see clinical efficacy measures)

The FAC has been found to have good predictive validity for community ambulation after stroke (FAC ≥ 4 predicts community ambulation at six months with 100% sensitivity and 78% specificity) [38]. It is proposed that pedalling exercise might have a positive effect on walking and thus postulated that the ability to walk might influence the ability to pedal and respond to pedalling intervention.

8. Ability to control the trunk

As measured by the Trunk Control Test [37]. This is a short, simple measure of motor loss developed for use after stroke. Patients are asked to do four movements-rolling to their weak side, rolling to their strong side, sitting up from lying down and balancing in a sitting position. Each movement is scored according to ability, either 0, 12 or 25, leading to a total score out of 100. Validity and reliability (comparison with Rivermead Motor Assessment at six, twelve and eighteen weeks post-stroke-Spearman's rho, *r*= 0.70, 0.72 and 0.79 respectively; interrater reliability, Spearman's rho, *r = *0.76, p < 0.001) have been established [37].

Balance (trunk) control is highly specific to ambulatory control, and makes a crucial contribution to the ability to perform activities of daily living [41]. The Trunk Control Test has been found to be a predictor of functional outcomes after stroke, including significant correlation with: discharge Functional Independence Measure (Pearson's *r *= 0.738) and gait velocity (Pearson's *r *= 0.654) [31]; and discharge walking ability (Spearman's rho = 0.71) [36]. It is possible, therefore, that trunk control early after stroke might influence the ability to perform rehabilitation activities and thus will be assessed as a potential prognostic indicator for pedalling exercise after stroke.

#### Adverse events

There is a small risk that for some people, UP might lead to an "overuse" syndrome, as expressed through an increase in pain or fatigue. We will monitor for this by checking for participant reports of lower limb pain, either verbal or behavioural. Intervention will cease and an adverse event recorded if a participant demonstrates a decrease of 2 or more minutes in ability to pedal on 2 consecutive treatment days, or a 25% reduction in mean rpm on 2 consecutive treatment days.

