## Aims

The driver for this proposed research is the hypothesis that UniCam crank-assisted upright pedalling (UP), used as an adjunct to conventional physical therapy, enhances recovery of lower limb motor function in stroke survivors with substantial paresis early after stroke. However, before this hypothesis can be tested in a phase III trial, it is important to establish whether there is sufficient evidence of benefit (clinical efficacy) to justify proceeding to subsequent larger trials and which stroke survivors are most likely to be able to participate in UP (prognostic indicators). Therefore, the aims for the current early phase clinical research study are:

1. Clinical Efficacy

To determine whether there is sufficient evidence for UP, balancing efficacy and potential adverse events (pain and fatigue), to justify proceeding to subsequent larger clinical trials; as assessed by:

a) ability to voluntarily contract paretic muscle;

b) production of reciprocal activation of antagonistic muscle groups during pedalling, similar to walking;

c) timing of onset and offset of activity in antagonist muscle groups during pedalling, similar to walking;

d) ability to walk independently.

2. Prognostic Indicators

To determine whether site of stroke lesion, trunk control ability, severity of lower limb paresis and/or ambulatory ability predicts ability to use UP within 30 days of stroke onset.

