#### Study procedure

All participants will undergo baseline measurement set 1 (prognostic indicators). They will then be assessed for their ability to perform UP. Potential participants will be taken to the treatment area and shown the cycling equipment. If content to proceed, a hoist will be used to seat them on the bike safely. They will be asked to pedal slowly for one minute to familiarise themselves with the equipment. They will then be asked to pedal for one further minute and a visual observation of whether they can pedal or not will be made.

Those unable to pedal and who are 31 days or more after stroke onset will be excluded from the randomised part of this trial. Those unable to pedal and who are 30 days or less after stroke onset will be offered further pedalling assessments approximately every three days. The rationale for further pedalling assessments is that, during the first 30 days after stroke, people may experience fear of movement or emotional distress and therefore may need more than one experience of pedalling within a therapeutic environment. Without repeated opportunities for pedalling assessment some participants may be excluded unfairly from the opportunity to participate in UP.

Those participants able to pedal for one minute and who are 30 days or less after stroke onset, will then undertake baseline measures set 2 (clinical efficacy). Participants will then be allocated randomly to either routine conventional physical therapy (CPT; control group) or to CPT plus UP (experimental group). Randomisation order will be generated before the trial begins by an independent statistician, in blocks of four. Group allocation will be concealed in sequentially numbered opaque sealed envelopes held by an independent administrator, who is not involved in the study and will have no contact with study participants. The next highest number envelope will be opened by the independent administrator in response to a telephone request from the research therapist. After opening, envelopes will be stored securely with the participants' study data. Randomisation will be concealed from the independent outcome assessor and participants will be asked not to discuss group allocation with the outcome assessor.

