#### Experimental Intervention

Participants allocated to the experimental group will receive UP in addition to CPT. All experimental participants will be asked to pedal at 50 revolutions per minute (50 rpm) at a comfortable resistance whilst maintaining a heart rate of 85% or below their age-predicted maximum (i.e. less than 220-age ×0.85 beats per minute). If patients cannot achieve 50 rpm, the research therapist will be guided by their response in setting the maximum rpm. The mean rpm achieved will be recorded for each participant for each intervention session. It is anticipated that few patients this early after stroke will immediately manage ten minutes of pedalling, so the number of minutes pedalled, up to ten minutes, will be recorded.

Each intervention session will also involve recording: the pedal crank setting; the degree of reciprocal activation of antagonistic muscle groups (see measurement battery); the timing of onset and offset of activity in antagonistic muscle groups (see measurement battery); and the distance pedalled (m). This description of each intervention session will allow replication of the intervention and information on how to progress the intervention over time in subsequent clinical trials.

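### Aim 1 weighs efficacy against pain and fatigue, but the stated overuse criteria rest on pedalling and no collection in controls is stated, so pedalling-arm events have no background rate

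*Protocol article*

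**What the plan says.** All references are to the Protocol article.

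- **Aims, item 1.** Whether upright pedalling (UP) merits larger trials is to be judged by "balancing efficacy and potential adverse events (pain and fatigue").
- **Adverse events.** UP might cause overuse, "as expressed through an increase in pain or fatigue". This is to be watched for by "checking for participant reports of lower limb pain, either verbal or behavioural". Pedalling stops and an adverse event is recorded when either of two criteria is met. The first is "a decrease of 2 or more minutes in ability to pedal on 2 consecutive treatment days". The alternative, resting on cadence instead of duration, is worded "or a 25% reduction in mean rpm on 2 consecutive treatment days". No other criterion for recording an event is given, and the reference day for a decrease is not stated.
- **Control intervention.** Controls have conventional physical therapy (CPT) alone.
- **Discussion.** The research team will monitor and record signs of fatigue. This is offered as an answer to the difficulty of pedalling so soon after stroke.
- **Study procedure.** "Those participants able to pedal for one minute", and who are within the time window, go on to randomisation. The Experimental Intervention section expects few to manage ten minutes at first.
- **Experimental Intervention.** The heart-rate limit is given in words, "maintaining a heart rate of 85% or below their age-predicted maximum", and then as a formula, "less than 220-age ×0.85 beats per minute".

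**The concern.** Efficacy is to be compared between arms, while the harm side of the same balance is tied to measurements that only one arm produces. Pain and fatigue can occur after stroke whatever therapy is given. If they are counted only where there is pedalling, every event in the UP arm reads as a cost of UP, and nobody can say how many would have occurred under CPT alone. Aim 1 could then be answered wrongly in either direction. Background symptoms might be blamed on UP, or the investigators might dismiss a real excess as background with no data to check that.

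There are two lesser concerns. An absolute fall of two minutes fits poorly with an entry test of one minute. The heart-rate formula, taken as printed, disagrees with the words beside it.

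**Working it through.** **1. Can a control meet an event criterion?**

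| Item | UP arm | Control arm |
|---|---|---|
| Minutes pedalled per treatment day | recorded each session | none |
| Mean rpm per treatment day | recorded each session | none |
| Pain reports | checked, as a sign of overuse from UP | collection not stated |
| Fatigue | monitored, in the context of pedalling; no measure named | collection not stated |

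Both criteria need values on two consecutive treatment days. Controls may pedal at baseline and outcome assessment for the EMG measures, but they have no pedalling treatment days between. Their count of rule-defined events is therefore 0 whatever their true level of pain and fatigue. For the pain check, the sentence refers back to overuse that UP might cause, and no rule says when a pain report is recorded as an adverse event.

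**2. Who can meet the minutes criterion?** Let b be the reference duration in minutes. A fall of at least 2 requires b ≥ 2. If the rule means a further 2-minute fall on each of two successive days, it requires b ≥ 4.

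| b (min) | Fall of 2 possible? | Two successive falls of 2 possible? | 2 min as a share of b |
|---|---|---|---|
| 1 | no | no | over 100% |
| 1.5 | no | no | over 100% |
| 2 | only by not pedalling at all | no | 100% |
| 3 | yes | no | 2/3 = 67% |
| 4 | yes | only by not pedalling at all | 2/4 = 50% |
| 10 | yes | yes | 2/10 = 20% |

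The rpm criterion is relative, so it can be met at any cadence: 50 × 0.75 = 37.5, 30 × 0.75 = 22.5, 20 × 0.75 = 15 rpm.

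**3. Heart-rate wording against formula.** With age a:

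- Words: 0.85 × (220 − a) = 187 − 0.85a.
- Formula as printed, by ordinary operator order: 220 − 0.85a.
- Difference: 220 − 187 = 33 beats per minute at every age.
- Formula minus the age-predicted maximum: (220 − 0.85a) − (220 − a) = 0.15a, which is always positive.

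| Age | Words | Formula as printed | 220 − age |
|---|---|---|---|
| 50 | 144.5 | 177.5 | 170 |
| 70 | 127.5 | 160.5 | 150 |
| 80 | 119.0 | 152.0 | 140 |

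**4. Scale, used only to cost the fix.** The plan's sample size reproduces: 2 per month × 12 months = 24. If all 24 could pedal and allocation were equal (an assumption), there would be 24 / 2 = 12 controls. Over at most 10 working days that is 12 × 10 = 120 brief checks.

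**The case against.** The best defence is that the two performance criteria say when pedalling stops, and a rule for stopping pedalling can only apply to people who pedal. A control count of zero on such a rule is then no flaw in the rule. Aim 1 asks whether the evidence supports UP on balance and promises no between-arm test of event counts. This is also a journal article, and a fuller protocol may hold the event forms and the control-arm schedule.

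Much of this stands. The criteria may serve well enough as stopping rules, and the point makes no complaint of that use. What does not fall away is that the same sentence is the only stated route by which an overuse event is recorded, while the Aims give those events weight in the decision to proceed. The article fixes both of these itself.

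Four stronger readings are tempting, and the document does not support them.

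- *Controls cannot have any adverse event.* This is true only of the two performance criteria. The pain check does not depend on pedalling measurements and is not expressly confined to one arm, and the Discussion mentions fatigue monitoring. The gap is that collection in controls is not stated.
- *The weakest pedallers are left without any criterion.* The relative rpm criterion is joined to the minutes criterion by an or, so it remains open to them. The one-minute test is also a threshold and follows a minute of familiarisation. Nothing shows how many would train below 2 minutes.
- *A change of crank or resistance would set off the rpm criterion.* This is speculative. Crank setting and mean rpm are recorded at each session, so a fall linked to the crank could be identified.
- *The printed heart-rate formula removes any limit on effort.* The worded limit stands in the same sentence. A bracket lost in print is the likely explanation.

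**Conclusion.** The main point holds as a weakness of design. As written, the plan gives no background rate of pain and fatigue for an aim that weighs them. Rule-defined events in controls are 0 by construction, and neither the pain check nor the fatigue monitoring is stated to extend to controls. This rests on two assumptions: that controls have no pedalling treatment days, and that no fuller document, not shown here, already provides for collection in both arms. If one does, the point reduces to saying so in the article.

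The minutes criterion is a secondary misfit. It cannot be met below 2 minutes of pedalling, or below 4 on the stricter reading, although 1 minute qualifies for randomisation. The number of participants affected cannot be estimated from the document.

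The heart-rate point is minor. The 33 beats per minute is exact for the formula taken literally, and the matter is one of wording.

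**What to change.** Record lower-limb pain reports and a simple fatigue rating in both arms, by the same method and on the same days. State how a pain report comes to be recorded as an adverse event, in the same terms for both arms. Report pain and fatigue by arm beside the efficacy result. Report the pedalling-performance events separately, as a description of the UP arm only.

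The clinical team should reconcile the one-minute test in Study procedure with the minutes criterion in Adverse events, and state the reference day and whether one fall or two successive falls are meant. The heart-rate formula in Experimental Intervention should be reconciled with the words beside it. No clinical limit or stopping rule is proposed here.

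The cost is a short daily check for controls, at most about 120 in all on the assumptions above, plus wording changes. Whoever makes the checks will know the allocation unless they are given to the blinded assessor, so the method should be scripted to keep it alike in both arms.
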